## Data Monitoring

*Item 21a: Composition of data monitoring committee (DMC); summary of its role and reporting structure; statement of whether it is independent from the sponsor and competing interests; and reference to where further details about its charter can be found, if not in the protocol. Alternatively, an explanation of why a DMC is not needed.*

The Data Safety and Monitoring Board is composed of independent researchers who are not associated with the project but who nevertheless have expertise in clinical or medical research. All members of the Data Safety and Monitoring Board are listed in the table below.

| Name | Institution / Position | Adress |
| --- | --- | --- |
| [name]. [name] | Dresden University of Technology  Institute of Clinical Psychology and Psychotherapie; Chair of Behavioural Psychotherapie | [name]  [name] |
| Apl. [name]. [name] | University Hospital Ulm  Senior psychologist of the child and adolescent psychiatry department | [name] |
| Univ.-[name]. [name] | Free University of Berlin  Professor at the department of Clinical psychology and psychotherapy | [name]  [name] |
| Apl. [name]. [name] | University Hospital Tuebingen. Senior physician at the department of Psychiatry and Psychotherapy | [name]  [name] |

*Item 21b: Description of any interim analyses and stopping guidelines, including who will have access to these interim results and make the final decision to terminate the trial.*

There will be no interim analysis

## Harms

*Item 22: Plans for collecting, assessing, reporting, and managing solicited and spontaneously reported adverse events and other unintended effects of trial interventions or trial conduct.*

Adjustments to the study or discontinuation of the entire study will be discussed regularly with the independent Data Safety and Monitoring Board in light of reported Adverse Events (AE) or Serious Adverse Events (SAE).

Adverse events (AE) describe any deterioration in the mental or physical condition or behavior of a participant administered the intervention, including events not necessarily caused by or related to the intervention. Following this definition, the following categories are defined as AE for the purposes of this project:

- Onset of new psychological symptoms
- Significant worsening of pre-existing psychological symptoms
- Occurrence of new physical symptoms
- Significant worsening of pre-existing physical symptoms
- Injuries that result in not being able to perform any sports activity for at least 2 months
- Covid-19 infections

A serious adverse event (SAE) is any adverse event that results in death, is life-threatening, requires inpatient hospitalization or prolongation of an existing hospital stay, or results in persistent or significant disability/incapacity. Other significant events may also be considered serious if they endanger the participant or require interventions to prevent any of the above mentioned consequences. Consequently, the following events are considered SAE under this project:

- Suicide
- Suicide attempt
- Other event that resulted in death
- Intentional serious self-injury that resulted in an inpatient stay
- Third party injury
- Event that is acutely life-threatening (i.e., study participant is in acute danger of death)
- Event that results in significant physical disability
- Hospitalization due to psychiatric and somatic symptoms

The above-mentioned categories of AE are recorded during the structured assessments (post, follow-up) via online questionnaires. In addition, participants and therapists (in the case of spontaneous reports by patients) have the opportunity to report AEs to a study telephone (available daily from 9 a.m. to 5 p.m.) at the central office at the University of Tuebingen. Employees of the study center document AEs in a CRF.

Based on the above list, SAEs are recorded by the exercise therapists during the intervention phase and reported to employees of the central office of the University of Tuebingen. In addition, SAEs will be collected by employees of the University of Tuebingen at all three measurement time points (pre, post, follow-up) for the intervention and control groups. They then report SAEs to the study director ([name]), who consults an independent Data and Safety Monitoring Board for further action within 12 hours after the SAE. The Data Safety and Monitoring Board is composed of independent researchers who are not associated with the project but have expertise in clinical or medical research. All members of the Data Safety and Monitoring Board are listed above. The Data Safety and Monitoring Board decides within 24 hours on any actions that may be necessary (e.g., changes in the trial or similar) and passes these on to the study director. All information on AEs and SAEs will also be recorded in the RedCAP system, like all other data collected.

The following data is documented for each AE/SAE:

- Pseudonym of participant
- Study site to which the participant was associated
- Date of start of SAE and associated study phase (pre, intervention phase, post or follow-up)
- Description of the SAE
- information on whether there was a risk for other participants
- Severity (rated by PI and DSMB)
  - **Mild** – Events require minimal or no treatment and do not interfere with the participant’s daily activities.
  - **Moderate** – Events result in a low level of inconvenience or concern with the therapeutic measures. Moderate events may cause some interference with functioning.
  - **Severe** – Events interrupt a participant’s usual daily activity and may require systemic drug therapy or other treatment. Severe events are usually potentially life-threatening or incapacitating. Of note, the term “severe” does not necessarily equate to “serious”.
- relationship to study intervention (rated by PI and DSMB)
  - **Related** – The AE is known to occur with the study procedures, there is a reasonable possibility that the study procedures caused the AE, or there is a temporal relationship between the study procedures and the event. Reasonable possibility means that there is evidence to suggest a causal relationship between the study procedures and the AE.
  - **Not Related** – There is not a reasonable possibility that the study procedures caused the event, there is no temporal relationship between the study procedures and event onset, or an alternate etiology has been established.
- expectedness
  - as rated by the Data Safety and Monitoring Board
- reporting events to participants
  - yes/no
- Date SAE ended
- Status at end of SAE (resolved, improved, not improved, consequences/type of harm)

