### Assessments to ensure internal validity

***Symptom severity at randomization.*** Symptom severity might change or fluctuate from the diagnostic interview or pre-assessment to the start of the intervention. In order to ensure clinically relevant transdiagnostic and disorder-specific symptomatology with the start of the intervention, scales that assess all primary and secondary outcomes will be presented again between randomization and group start: BSI-18 (Derogatis & Fitzpatrick, 2004), ISI (Dieck et al., 2018; Morin, 1993), PSQI(Buysse et al., 1989), PHQ-9 (Kroenke et al., 2001; Spitzer et al., 1999), GAD-7 (Lowe et al., 2008; Spitzer et al., 2006), PCL-5 (Kruger-Gottschalk et al., 2017).

**(Serious) Adverse Events.** Adverse events (AE) will be assessed at pre, post-1, and follow-up assessment. AEs and Serious Adverse events (SAEs) can be further reported by patients or therapists at a central phone number. AEs and SAEs will be documented and SAEs will be reported to an independent Data Safety and Monitoring Board, which will discuss adjustments to or discontinuation of the entire study**.**

**~~Treatment Fidelity (adherence to protocol of study therapists).~~** ~~Core elements of the manualized ImPuls intervention have been determined a priori. All inhouse sessions (see fig. 3 and table 1) of all therapists at all study sites will be video-taped despite outdoor MVAE. External research assistants will be trained to rate fidelity based on deliverance as intended in the manual. A treatment fidelity score will be determined as a mean of all ratings. 10 % of all video-taped sessions will be randomly selected and analyzed. A fidelity score of ≥ 90 % is assumed~~.

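### AEs are defined only for intervention recipients, SAEs are actively recorded between assessments only in ImPuls, and the AE time points and the 12-hour clock do not fit the rest of the protocol

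*Protocol*

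**What the plan says.** **Definition.** Harms (Item 22) words an AE as "any deterioration in the mental or physical condition or behavior of a participant administered the intervention". An SAE is then defined as an adverse event with certain serious consequences, so it inherits the same population. Later in Item 22, SAEs are to be collected by university staff at pre, post and follow-up in the intervention and control groups.

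**Routes between assessments.** Item 22 states that "SAEs are recorded by the exercise therapists during the intervention phase and reported to employees of the central office". A study telephone, staffed from 9 a.m. to 5 p.m., is open to participants and therapists with no restriction by arm. Assessments to ensure internal validity and Data Management (Item 19) agree that notification may come from the participant or the therapist.

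**AE time points.** Assessments to ensure internal validity says "Adverse events (AE) will be assessed at pre, post-1, and follow-up assessment". Item 22 says "The above-mentioned categories of AE are recorded during the structured assessments (post, follow-up) via online questionnaires", without pre.

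**Clock.** SAEs go to the study director, "who consults an independent Data and Safety Monitoring Board for further action within 12 hours after the SAE". Recruitment (Item 15) places post and follow-up six and 12 months after randomisation.

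**The concern.** Four provisions do not fit together.

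- The stated definition leaves out the control arm, although control-arm SAEs are to be collected.
- One arm has a designated SAE recorder between assessments and the other does not. If all reports are put into one table, the arm with more listening posts shows more events even when true rates are equal.
- The two sections disagree on a baseline AE assessment. Four of the six AE categories turn on whether a symptom is new or a worsening of an existing one, so without a pre assessment that distinction rests on recall over about six months.
- The 12-hour limit runs from the event, while the protocol's own collection schedule may first reveal the event months later.

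Item 22 has the monitoring board discuss adjusting or discontinuing the study in light of reported AEs and SAEs. Unequal capture would therefore reach decisions made during the trial as well as the final report.

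**Working it through.** The protocol states no harm rate, so there is no figure of its own to reproduce. The check compares the sections and adds three small calculations.

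**1. Definition against collection.** Read literally, Item 22's AE definition, and hence its SAE definition, covers only people who receive ImPuls. The same section collects SAEs in the control group and allows pre as the study phase of an event, before anyone has received ImPuls. The wording and the procedure cannot both be right.

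**2. Therapist contacts before post, ImPuls only.**
- In-house sessions: 10 (Qualitative Data, fidelity paragraph).
- Weekly calls, weeks 5 to 12: 8 (Interventions, Item 11a).
- Biweekly calls, weeks 13 to 24: 12 / 2 = 6 (same place).
- Total: 10 + 8 + 6 = 24. TAU: 0.

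These are occasions on which an SAE can surface. No section says that SAEs are asked about at each one. TAU patients can telephone, but that route is passive. The SAE list also includes deaths, which the patient cannot report, and no other reporter is named for TAU between assessments.

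**3. What pooling over sources could do.** Assume equal true SAE rates. Let s be retention at the structured assessment, q the chance that a retained patient reports the event there, and c the chance that a therapist captures it in ImPuls, independently of the structured assessment. Telephone reports are ignored. Then

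apparent ImPuls/TAU ratio = [1 − (1 − sq)(1 − c)] / (sq).

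Here s = 0.70 matches the 30% dropout assumed under Sample Size. All values of q and c are assumptions.

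| s | q | sq | c = 0.25 | c = 0.75 |
| --- | --- | --- | --- | --- |
| 1.00 | 0.8 | 0.80 | 0.85/0.80 = 1.06 | 0.95/0.80 = 1.19 |
| 0.70 | 0.8 | 0.56 | 0.67/0.56 = 1.20 | 0.89/0.56 = 1.59 |
| 0.70 | 0.5 | 0.35 | 0.5125/0.35 = 1.46 | 0.8375/0.35 = 2.39 |

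If only structured-assessment events are compared (c = 0), the ratio is 1.00, given equal retention and recall in both arms. With complete retention and recall (sq = 1) it is also 1.00 whatever c is.

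**4. The clock.** An SAE first disclosed at the six- or 12-month assessment will almost always be more than 12 hours old, in either arm. In ImPuls, an SAE that surfaces at a call can also be too old, since calls are 7 or 14 days apart. Even immediate telephoning does not always help: an SAE starting between 17:00 and 21:00 has a 12-hour window that closes between 05:00 and 09:00, with the line shut throughout. That is 4/24 = 16.7% of onset times if onset is uniform over the day, in both arms.

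**The case against.** Four stronger conclusions are tempting, and the document does not support them.

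- **A reader might infer that harms are recorded between assessments only in ImPuls.** They are not. Three sections give participants a notification route with no restriction by arm. What is confined to ImPuls is active recording, and Item 22 states it for SAEs; for other AEs, therapists pass on what patients volunteer.
- **A reader might infer that TAU events cannot meet the 12-hour limit.** A TAU SAE telephoned in promptly can meet it, and an ImPuls SAE can miss it. The limit also governs when the board is consulted, not whether an event is counted. It could be loose wording for 12 hours after the report, but the text says otherwise.
- **A reader might infer that the definition leaves TAU with no AEs.** The procedures do not apply it that way: SAE collection names the control group, and the AE questionnaire carries no arm restriction.
- **A reader might infer that harm rates cannot be compared between arms.** SAEs are collected in both groups on one schedule, and AE categories by questionnaire at post and follow-up, so a like-for-like comparison is available.

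It is also fair to say that the protocol announces no between-arm harm test and no pooling of sources, that tabulation of harms is commonly left to the analysis plan, and that the AE categories and recorded start dates partly separate new from existing complaints.

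What stands is what the protocol itself fixes: the definition, the unequal SAE routes, the conflicting time points and the start of the clock. The items documented for each event do not include how it came to light, so an analysis plan could not be sure of separating sources afterwards.

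**Conclusion.** The concern holds in a limited form. The AE and SAE definitions are wrong as written for a two-arm trial. The two sections contradict each other on AE assessment at pre. The 12-hour limit, counted from the event, does not fit SAE collection at the six- and 12-month assessments; this is a general reporting flaw in both arms and does not itself distort harm rates.

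The statistical consequence is confined to SAE counts pooled over sources, including those that reach the monitoring board. There the direction is towards more recorded SAEs in ImPuls. The size is unknown: the ratios of 1.06 to 2.39 rest on assumed recall and capture and illustrate the mechanism only. The 24 contacts all fall before post, so no such asymmetry is shown for months six to 12. No efficacy hypothesis, sample size or primary analysis is affected.

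**What to change.** 1. Define AEs and SAEs for every randomised participant, regardless of arm or of treatment received.
2. Reconcile Assessments to ensure internal validity with Item 22 on whether AEs are assessed at pre, and use the same questions in both arms at each time point.
3. Base the between-arm harm comparison on events solicited identically in both arms at the structured assessments. Record the source of each report, and tabulate therapist- and telephone-reported events separately by source, for the monitoring board as well.
4. Reconcile the start of the 12-hour limit with collection at six and 12 months, for example by counting from when the central office becomes aware of the SAE.

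The cost is protocol wording, a source entry for each event and at most one questionnaire block at pre. Spontaneous and therapist reports leave the arm comparison but are still reported, so no safety information is lost.

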Despite the promising evidence for MVAE as an intervention for patients with mental disorders, exercise programs or professional exercise therapy are currently not provided as regular health services within the outpatient mental health care system in Germany. With the aim of combining the current evidence on the efficacy of MVAE and sustained exercise behavior change with specific demands of a real-world outpatient health care setting, ImPuls was developed as a manualized group exercise intervention (Wolf et al., 2020; Zeibig et al., 2021) for physically inactive outpatients suffering from major depressive disorders, insomnia, panic disorder with or without agoraphobia and PTSD. ImPuls integrates recent findings about the optimal modalities of exercise for therapeutic efficacy, such as optimal frequency, intensity, time/duration and type of exercise (FITT criteria) for the targeted disorders and evidence regarding sustainable behavior change by integrating behavior change techniques (BCTs). The components of this intervention are further tailored towards the specific needs of outpatients with mental disorders in the current German mental health care setting. Specific features are 1) the inclusion of a broad range of heterogenous diagnoses for which prior research has demonstrated therapeutic efficacy, 2) intervention delivery in group format, and 3) short duration (i.e., only 4 weeks of supervised MVAE sessions carried out inhouse in each study site). The aim of the current study is to investigate the efficacy and cost-effectiveness of implementing ImPuls within the outpatient mental health care setting in Baden-Württemberg, a representative state in South-West Germany. The following hypotheses will be tested:

1. Participants in the intervention condition, who have received ImPuls in addition to TAU, will show lower global symptom severity at post-treatment and follow-up assessments compared to a control condition with TAU only.

2. Overall costs in the intervention condition will represent a significant saving for the public health system compared to the control condition at post-treatment and follow-up assessments.

3a. The intervention will lead to significantly higher levels of MVAE at post-treatment and follow-up assessments compared to the control condition.

3b. The effect of condition on the reduction of the primary outcome global symptom severity will be mediated by an increase in MVAE.

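### The only adverse-event category that names injuries requires at least 2 months without any sport, so the trial's injury count will omit shorter exercise injuries

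*Protocol*

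**What the plan says.** All the AE wording is in the protocol's Harms section (Item 22). The general definition has no minimum duration or severity: "Adverse events (AE) describe any deterioration in the mental or physical condition or behavior of a participant administered the intervention". The section then makes a list operative: "Following this definition, the following categories are defined as AE for the purposes of this project". Three of its six categories matter here:

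- "Occurrence of new physical symptoms", with no threshold of any kind.
- "Significant worsening of pre-existing physical symptoms", with a severity qualifier but no duration.
- "Injuries that result in not being able to perform any sports activity for at least 2 months", the only line that names injuries and the only one with a duration threshold.

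The same section says that these categories are what the online questionnaires record at post and follow-up, with telephone reporting available in addition. The list of serious AEs (SAEs) covers hospitalisation, significant physical disability and acute danger to life, none with a 2-month condition. The severity scale begins at Mild: "Events require minimal or no treatment and do not interfere with the participant’s daily activities".

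On the intervention, the Introduction (Item 7) describes "only 4 weeks of supervised MVAE sessions carried out inhouse in each study site". The Interventions section labels the supervised period weeks 0-4, has patients run or walk fast, and continues with partly supervised exercise to week 24. The eligibility criteria exclude people who already exercise regularly.

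**The concern.** The programme has physically inactive patients take up running or fast walking, so injury is a foreseeable physical harm. Yet the line written for it has the strictest entry rule on the list: all sport must be impossible, and for at least 2 months. The definition it is meant to put into practice has no such bar.

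Two things are at stake. The first is the injury count itself, which a reader of the trial report would take as the number of injuries. The second is the comparison between arms. Any missing exercise injuries would probably come mainly from the arm assigned to exercise, so an incomplete count would tend to make the intervention look safer. The Data Safety and Monitoring Board discusses changes to the study or its discontinuation in the light of reported AEs, and later decisions on wider implementation would draw on the same data.

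**Working it through.** The protocol gives no figure for injury frequency or duration, so there is none to reproduce. The check is duration arithmetic plus a comparison of the list's lines.

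**Duration**

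- Threshold (Harms): 2 months × 30.4 days = about 61 days; 61 / 7 = 8.7 weeks.
- Supervised phase (Introduction, Item 7): 4 weeks. 8.7 / 4 = 2.2.
- Supervised phase if weeks 0-4 (Interventions) are counted as five weeks: 8.7 / 5 = 1.7.
- Whole programme (Interventions): 24 weeks. 8.7 / 24 = 36%.

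The threshold is longer than the supervised phase on either count.

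**A worked case.** A patient is injured at the start of week 1 and cannot exercise for 8 weeks. Eight weeks is 56 days, short of 61, so the injury line is not met. With two supervised sessions a week, weeks 1-4 contain 4 × 2 = 8 sessions, all missed. That exceeds the limit of four in a row in Item 11b, so a patient who continues the assessments is classed as a treatment-dropout. An injury that costs most of the intended supervised exercise is not an injury under the AE list.

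**The word any.** A patient who cannot run for six months but can cycle is still able to do some sport, so read literally the line is not met.

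**Timing.** An injury that begins in the last 8.7 weeks before the post questionnaire cannot yet have met the rule when the patient answers. It can have met it by follow-up, about six months later. Only injuries that begin in the last 8.7 weeks before follow-up cannot qualify at any questionnaire.

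**The lines side by side.** The list can be read in two ways:

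1. The injury line governs injuries. Then shorter injuries are not AEs, which contradicts a definition covering "describe any deterioration in the mental or physical condition or behavior of a participant".
2. Injuries may also be entered under "Occurrence of new physical symptoms" or "Significant worsening of pre-existing physical symptoms". Then a shorter injury can be an AE, but it is filed as a symptom and does not appear as an injury.

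The protocol does not say which reading applies. Under both, the injury category omits shorter injuries. They differ only on whether those events reach the AE total, and that is left to how each patient reads the questionnaire.

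**The case against.** The strongest reply is that the list is a set of alternatives. A sprain that causes new pain or swelling is a new physical symptom, and that line has no threshold. An injury leading to hospitalisation or significant disability is an SAE whatever its length. Follow-up can pick up injuries that began shortly before post. Therapists call absent patients, telephone patients regularly from week 5 and can pass on what they hear, and dropouts are asked for their reasons. Listing long-lasting injuries on a separate line beside broad symptom categories could also be a deliberate way to flag the important ones.

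Much of this stands, and it rules out several stronger readings that a reader might infer:

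- **That most exercise injuries would not be counted.** The symptom and SAE routes are open, and the documents contain no injury data. One could assume exponential time off sport with a median of 2, 3 or 6 weeks. The share lasting 8.7 weeks or more is then 2^(-8.7/median) = 5%, 13% or 37%, which puts 63% to 95% outside the injury line. Neither the shape nor the medians come from the protocol, and the result is the share outside one category, not the share missing from AE recording.
- **That a qualifying injury could only be graded Severe.** The grades turn on treatment and daily functioning, not sport, and the Moderate grade allows some interference with functioning.
- **That the wording was chosen to support the Introduction's expectation that exercise causes few adverse effects.** That is general background, and nothing links it to this line.
- **That the two arms are asked different questions.** The questionnaire is not part of the document, so no difference is shown.

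The reply does not repair the list. If the symptom lines are meant to take all injuries, the threshold does no work except to remove shorter ones from the only category labelled as injury. If they are not, shorter injuries are lost. The protocol does not describe the line as a flag for notable injuries, and the other routes do not yield a count of injuries.

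**Conclusion.** The point holds for the injury category, not for AE recording as a whole. As written, an injury enters that category only if all sport is ruled out for about 8.7 weeks or longer. That is narrower than the protocol's own definition of an AE and overlaps two symptom categories without explanation. The injury count will therefore be incomplete. Shorter injuries are either absent from the AE data or dispersed among physical symptoms and, for a few, SAEs.

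The size of the shortfall cannot be computed from the documents. That it would fall mainly in the exercise arm is a judgement, resting on the assumption that patients assigned to running or fast walking have more exercise injuries than controls. The contradiction itself rests only on the wording and the duration arithmetic. It should be corrected because the line concerns a foreseeable harm of the intervention and the correction is small.

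**What to change.** Reconcile the lines of the AE list in Harms:

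- Replace the injury line with a recording category for any injury, without a duration condition.
- For each injury record the onset date, whether it arose during exercise, and the number of days unable to exercise.
- Report injuries of 2 months or longer as a predefined subset, so that what the present line isolates is kept.
- State that an injury is entered under the injury category and not again as a physical symptom, so that it is counted once.
- State that the same wording is used in both arms. This is a safeguard, not a correction of a difference shown in the documents.

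The cost is one changed line in the protocol and a few extra fields in the AE questionnaire and case report form. The downside is a higher, less favourable AE count. If some questionnaires have already been answered under the present wording, the report should say which wording each patient received.

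### The SAE list that therapists record against is narrower than the protocol's own SAE definition: disability is limited to physical disability, and prolonged hospital stays are left out

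*Protocol*

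**What the plan says.** All of the main text is in the protocol under Harms (Item 22).

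- **Definition.** An SAE is an adverse event that is fatal or life-threatening, that "requires inpatient hospitalization or prolongation of an existing hospital stay, or results in persistent or significant disability/incapacity". A further sentence adds an optional category: "Other significant events may also be considered serious if they endanger the participant or require interventions to prevent any of the above mentioned consequences".
- **Project list.** The list is introduced by "Consequently, the following events are considered SAE under this project" and has eight items. Nothing marks them as examples. The disability item reads "Event that results in significant physical disability" and the admission item reads "Hospitalization due to psychiatric and somatic symptoms".
- **Who uses the list.** "Based on the above list, SAEs are recorded by the exercise therapists during the intervention phase". Separately, central study staff collect SAEs at pre, post and follow-up in both arms; no criteria are stated for that route.
- **What SAE status triggers.** The study director consults the Data Safety and Monitoring Board within 12 hours of the event, and the board decides on action within 24 hours.
- **Where other mental deterioration goes.** The AE categories in the same section include "Significant worsening of pre-existing psychological symptoms".

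**The concern.** A project list that claims to follow from a definition should catch every event the definition makes serious. This one does not, and the gap falls where it matters for the population. Participants are enrolled for depressive disorders, agoraphobia, panic disorder, PTSD or insomnia (Eligibility Criteria), so a serious non-fatal harm may well be mental. The protocol's AE definition covers both mental and physical deterioration, and its AE list has entries for each. The disability item of the SAE list keeps only the physical side.

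At stake are the classification of such events, the speed with which the safety board is consulted, and the meaning of the reported SAE count, which would depend on whether the definition or the list was applied.

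**Working it through.** No arithmetic applies beyond a count. The check sets each criterion of the definition against the eight list items and then asks which of the two texts is used for recording.

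| Criterion in the definition | Matching list item | Result |
|---|---|---|
| Death | Suicide; other fatal event | Covered |
| Life-threatening | Acutely life-threatening event | Covered |
| Inpatient hospitalisation | Hospitalisation for psychiatric and somatic symptoms; self-injury leading to an inpatient stay | Covered |
| Prolongation of an existing stay | None | Absent |
| Persistent or significant disability/incapacity | Significant physical disability only | Narrowed |
| Other significant events (optional) | No general item | No contradiction, because the definition says these *may* count |

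Of the five mandatory criteria, three are covered, one is absent and one is narrowed (3 + 1 + 1 = 5).

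**What the narrowing removes.** Three things go: non-physical disability, incapacity as a separate term, and disability that is persistent without being judged significant.

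**Test case 1.** A participant's depression or PTSD worsens until he or she is persistently incapacitated, with no admission, no suicide attempt and no acute danger to life. Under the definition this is an SAE through the disability/incapacity criterion. No list item applies. Under the AE list it is a significant worsening of existing psychological symptoms. The same event is therefore serious by one paragraph and non-serious by the next.

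**Test case 2.** A hospital stay is extended. If the stay began during the trial because of symptoms, the admission is already a listed SAE and no case is lost. The gap affects only a stay not itself reported as an SAE, for example a planned one.

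**Which text governs.** For therapists during the intervention phase the protocol points to the list. For central staff it does not say.

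**Consequence of the AE label.** The protocol asks for AE categories by questionnaire at post and follow-up, which the Recruitment section places six and 12 months after randomisation; the internal-validity section adds pre. There is also a study telephone line. An event in test case 1 that nobody phones in could wait for the next questionnaire, up to about six months (6 − 0 or 12 − 6), instead of entering the 12-hour and 24-hour route.

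**The case against.** Several stronger readings are tempting, and the protocol does not support them.

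- **That therapists will not report such events.** The text shows only that they are not instructed to report them as SAEs. Therapists and patients can phone in AEs and SAEs, and central staff collect SAEs at three time points by a sentence that is not tied to the list.
- **That the safety board would never see them.** Harms says that changes to the study are discussed regularly with the board in the light of reported AEs as well as SAEs. Severity and relationship are documented for each AE or SAE and rated by the principal investigator and the board. The *severe* grade expressly includes incapacitating events. What is lost is the SAE label and the expedited consultation. Severity grading does not restore these, because the protocol notes that severe does not necessarily mean serious.
- **That a purely psychiatric admission fails the list because of the word *and*.** The ordinary reading of "Hospitalization due to psychiatric and somatic symptoms" is that both kinds of admission count. The wording is loose, but the criterion is covered.
- **That the Introduction's national sick-leave figures show the dropped category to be common.** Those are population days of incapacity to work. They are neither an event rate in trial participants nor a count of disability in the SAE sense.
- **That the list is narrower throughout.** It is not. "Third party injury" goes beyond the core criteria, and suicide attempt is listed without any condition of hospitalisation.

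It is also fair to say that prolongation has little practical weight in an outpatient trial, that the missing general item contradicts nothing, and that the list does not differ by arm. None of this removes the mismatch on disability and incapacity.

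**Conclusion.** The point holds as an inconsistency within the Harms section. One mandatory criterion is materially narrowed (disability/incapacity), and one is absent with minor effect (prolongation). Followed as written, a non-hospitalised, persistent mental incapacity that meets the protocol's definition is handled as an ordinary AE and misses the expedited consultation, although it remains open to AE review and rating by the board. The SAE count then depends on which paragraph is applied.

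This rests on two readings: that the list is meant to be complete, since nothing labels it as examples, and that therapists follow the list as told. The number of events affected cannot be derived from the documents. No effect on the efficacy analysis is claimed. The correction is worth making because it concerns safety classification in a trial of mental disorders and is cheap.

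**What to change.** Reconcile the list with the protocol's own definition in one of two ways:

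1. Reword the disability item so that it is not limited to physical disability and covers persistent or significant disability or incapacity, and add prolongation of an existing hospital stay.
2. Label the list as examples, and change the recording instruction so that therapists record SAEs against the definition.

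Either way, state that central staff use the same criteria at pre, post and follow-up. Optionally, replace *and* with *or* in the hospitalisation item. A general item for other significant events is a matter of choice.

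The cost is a wording update to the protocol, the case report form and the therapist instructions, and probably a few more SAE reports for the study director and the safety board to handle.
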